## Abstract

**Background**: Lithium is the gold-standard treatment for Bipolar Disorder (BD) in both adults and adolescents, effectively managing mood episodes and reducing suicide risk. While its efficacy in neurotypical youth is well established, its use in adolescents with Autism Spectrum Disorder (ASD) and comorbid BD remains under-researched. Here, we present the protocol for a study aiming to evaluate the efficacy and tolerability of Extended-Release Lithium Salts in treating adolescents with BD and comorbid ASD compared to neurotypical BD patients. **Methods**: This longitudinal prospective naturalistic comparative study will enroll lithium-naïve adolescents aged 12–18 with BD, with or without comorbid ASD, from the Department of Child and Adolescent Psychiatry and Psychopharmacology. Participants will be followed for six months while receiving Extended-Release Lithium Salts treatment. Primary outcomes will include mood instability, suicidality, emotional dysregulation, and aggression, assessed through a range of clinical rating scales and diagnostic tools at baseline, three months, and six months. Secondary outcomes will focus on the safety and tolerability of Extended-Release Lithium Salts, with measures including side effect ratings, physical exams, and laboratory tests. **Results**: We hypothesize that Extended-Release Lithium Salts will demonstrate non-inferiority in treating BD symptoms in adolescents with comorbid ASD compared to those without ASD. **Conclusions**: This study is poised to fill a significant gap in the literature by providing critical data on the use of lithium for adolescents with BD and ASD. Findings will inform clinical practice and future research, potentially guiding more personalized treatment approaches for this complex and vulnerable population.

## 1. Introduction

Lithium is the gold-standard medication for treating Bipolar Disorder (BD), providing significant clinical effectiveness against both depression and mania as well as in preventing mood episodes relapses and reducing the risk of suicide [1,2,3]. For children and adolescents, lithium has been approved by the major regulatory agencies, including the Food and Drug Administration (FDA) and the European Medicines Agency (EMA), for treating BD [4], which shows a high worldwide prevalence up to 3.4% [5]. Nonetheless, less evidence supports the efficacy of lithium in youth compared to adults [6,7,8,9].

A meta-analysis [10] on the treatment of pediatric mania found that lithium effectiveness was unclear, due to the lack of controlled studies at the time, with promising outcomes for second-generation antipsychotics (SGAs). A more recent review [2] found, instead, a level 1b of evidence for lithium on mania in pediatric BD (e.g., [7,11]), in line with the findings of an even more recent systematic review [12] suggesting that lithium is an effective and well-tolerated treatment for some forms of pediatric mania. Indeed, lithium is inferior in efficacy to Risperidone in prepubertal youths diagnosed with mania or mixed episodes and comorbid ADHD [12], while there is a lack of evidence concerning its efficacy and tolerability as acute treatment for manic symptoms in adolescents, and important clinical issues still remain unaddressed.

Less conclusive evidence is available for depression, with suggestive studies providing a level 2b of evidence (e.g., [13,14]). Other long-term studies support the use of lithium in relapse prevention of depressive episodes [6,8]. Interestingly, recent findings from large longitudinal studies suggest strong clinical benefits of lithium in reducing or preventing suicide risk in youth with BD, but these findings are not yet comprehensive. For instance, in 2019, the COBY study [15] examined more than three hundred youths with BD over ten years and found that patients on lithium had lower suicide attempts rates than those on other mood stabilizers. Similarly, a study conducted on Swedish national registries in 2023 [16] demonstrated that higher use of lithium was related to lower suicide rates compared to other treatments. Parasuicidal behaviors, including non-suicidal self-injury (NSSI), might also benefit from lithium treatment, although evidence is still scarce and based on cross-sectional studies [17,18].

Lithium is known to exert its anti-suicidal effects by preventing relapses of mood disorder, though additional mechanisms could also be considered, especially in youth. Indeed, there is some evidence that lithium reduces aggression and impulsivity, which is a possible mechanism mediating its anti-suicidal properties [1]. Adult patients taking lithium exhibit reduced self-harming and unintentional injury compared to those prescribed with Valproate, Quetiapine, or Olanzapine [19]. Lithium use prevents suicidality by decreasing impulsive aggression in addition to mood stabilization. Moreover, the effectiveness of lithium in preventing suicide is associated with decreased aggression and impulsivity, which are often associated with dysphoric, agitated, and mixed states, particularly vulnerable to suicidal events [20]. Additionally, it has been suggested that Lithium may promote its anti-suicidal properties via reinforcing top-down brakes of impulsive actions, and even natural lithium intake in drinking water can influence impulsivity and suicidality [21]. In line with this association, several studies found that lithium is effective in reducing impulsive aggression and temper outbursts in severely violent and hostile CD youth, being significantly superior to placebo [22] either in monotherapy or in add-on with atypical antipsychotics [23].

Lithium also remains commonly used for different psychiatric conditions in both adults and youths, either in or not in comorbidity with BD [2]. For instance, evidence is available for its use in Severe Mood Dysregulation [24], Major Depression as an augmenting medication [25,26], Conduct Disorder and aggression [22,27], Kleine–Levin Syndrome [28] and Fragile X Syndrome [29]. Within the context of neurodevelopmental disorders, lithium is warranted to minimize the risk of manic switch as well as suicidal and non-suicidal self-injurious behavior in ADHD youths with comorbid BD, especially when stimulants are prescribed [30,31,32]. Unfortunately, the use of lithium in people with Autism Spectrum Disorders (ASD) is still poorly investigated.

The association between ASD and BD in adult subjects has been repeatedly confirmed, and lithium has been suggested as the first treatment option for high-functioning ASD with comorbid BD [33]. Similarly, children and adolescents with ASD have high rates of comorbid BD, up to 4–7% in clinical cohorts [34,35], and often experience irritability, aggression, self-injury, and tantrums, as well as subclinical manic symptoms including elation, expansive mood, and racing thoughts [32]. Also, it is increasingly recognized that comorbid BD significantly contributes to the morbidity associated with ASD [36], although the communication difficulties and the frequently low intellectual functioning complicate the identification of comorbid clinical pictures in this population [37]. To further increase this clinical complexity, BD in ASD is often characterized by atypical features, such as irritability and behavioral disturbances, which are frequently associated with several other potentially comorbid conditions, including, above all, ADHD [37,38]. Finally, suicidal behaviors are also frequently observed in ASD-BD patients and may confer a greater risk of hospitalization [39,40] since ASD is an independent risk factor for suicide, with a probability to die by suicide which is ten times greater than in the general population [41].

Despite these considerations, research so far has only scarcely targeted this comorbid population to define guidelines for the clinical management of associated morbidity. Pharmacological treatment options available for ASD with comorbid BD are not directed to the core symptoms of the disorder but rather target challenging behaviors associated with comorbidities [32]. Second-generation antipsychotics (SGAs)—i.e., Risperidone and Aripiprazole—are currently approved by FDA and EMA for treating irritability and aggression in ASD youths [42]. Approximately 65% of ASD-BD patients treated with SGAs showed an improvement greater than 30% in irritability, and despite an atypical severity of BD symptoms in ASD youths, the presence of this comorbidity does not impact the relative rate of response [43]. However, given the high risk of SGA-related side effects, including weight gain and metabolic disorders, increased serum prolactin, and sedation, antipsychotics should be used cautiously [32].

On the other hand, lithium has been rarely studied in children with ASD, despite its established efficacy in controlling mood disorder symptoms in the neurotypical population, and controlled trials supporting its efficacy for mood instability, impulsivity, and cyclicity in ASD subjects are lacking. However, some case reports [44,45,46] and two retrospective chart reviews are available for this purpose [47]. In the first of these latter [48], 43% of ASD patients who received lithium improved after treatment, along with 71% of those who had two or more pretreatment mood disorder symptoms including mania and euphoria. In the second [49], 73.7% of patients with ASD experienced significant clinical improvement after add-on lithium salts to their treatment regimen, thus representing a reliable alternative to antipsychotics and other psychotropic medications.

Thus, the present article will present the research protocol for a longitudinal prospective study aiming to assess the efficacy and tolerability of Extended-Release Lithium Salts treatment in adolescents with ASD and comorbid BD versus neurotypical BD patients. This naturalistic comparative study will specifically focus on BD-related morbidity often associated with ASD, including suicidality, non-suicidal self-injury, irritability/emotional dysregulation (ED), and aggression in a longitudinal sample of referred youths with BD with and without ASD. In the absence of previous research on this topic, we hypothesize the non-inferiority of Extended-Release Lithium Salts in adolescent patients with BD and ASD compared with those without comorbid ASD.

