### 2.3. Procedure and Assessment

A matching number of BD patients with and without comorbid ASD will be recruited. The ASD-BD group will be the experimental arm of the study, with the BD-only group as the clinical comparator. Both groups will be followed up for six months after recruitment while receiving treatment with Extended-Release Lithium Salts for clinical indication. Primary and secondary outcome measures will be acquired before treatment initiation (T0), as well as three (T1) and six (T2) months after reaching stable drug dosage (Steady State—SS). At T0, patients will be screened for eligibility and carefully evaluated by means of the following diagnostic tools: the semi-structured DSM-5-based clinical interview Kiddie Schedule for Affective Disorders and Schizophrenia—Present and Lifetime version (K-SADS-PL); the Wechsler Intelligence Scale for Children—fourth edition (WISC-IV); the Autism Diagnostic Observation Schedule—second edition (ADOS-2); and the Autism Diagnostic Interview—Revised (ADI-R).

At each timepoint (T0, T1, and T2), patients will be thoroughly assessed as for clinical routine. The following rating scales will be filled in by clinicians based on parents’ and caregivers’ reports: the Clinical Global Impression (CGI) scale scores and the Children Global Assessment Scale (CGAS) scores. Patients will be also administered the following clinical interviews: the Children Depression Rating Scale (CDRS); the Young Mania Rating Scale (YMRS); the Columbia—Suicide Severity Rating Scale (C-SSRS); the Deliberate Self-Harm Inventory (DSHI); Reactivity, Intensity, Polarity and Stability questionnaire for Youth (RIPoSt-Y). Caregivers will be administered the following clinical rating scales: the Modified Overt Aggression Scale (MOAS) and the Affective Reactivity Index (ARI).

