### 2.5. Sample Size Calculation

Sample size has been estimated using G*Power software (version 3.1.9.7), considering the clinical rating scales described above as outcome measures of the study. Based on previous literature on BD youths treated with lithium [50], the YMRS score was the best available measure to determine the effect size that would be worth testing and thus was taken as the reference. The calculation was based on a repeated measures test between two independent mean differences of the main outcome, establishing the error level at 0.05, power at 0.95, and effect size at 1.06. Based on this setting, a sample size of 40 subjects (20 patients with ASD-BD and 20 BD-only controls) was obtained. However, since a dropout rate of 20% is expected after 6 months of follow-up based on our previous studies, 5 additional participants per group will be recruited, leading to a total number of 50 subjects as the final sample size (25 patients with ASD-BD and 25 BD-only controls).

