### 2.6. Statistical Analyses

Statistical analysis will be performed using RStudio^®^ (version 1.3.1093, RStudio, PBC, Boston, MA, USA). Non-parametric tests for repeated measures (e.g., Wilcoxon signed rank test) will be used to analyze the psychiatric assessment score variations of the clinical rating scales described above. Additionally, multiple linear regression models will be performed to detect the effect of the ASD diagnosis on the variations on patients’ clinical scores. Patients’ age and gender, ongoing treatment with other psychotropic drugs, and lithium plasma levels will be considered as covariates in multivariate analyses to account for possible specific effects.

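### The protocol hypothesises non-inferiority, but its stated analysis has no margin or confidence-interval rule and looks only for change over time and an ASD effect, so it cannot establish non-inferiority

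*Protocol article*

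**What the plan says.** The hypothesis appears twice. The Abstract expects that lithium "will demonstrate non-inferiority in treating BD symptoms in adolescents with comorbid ASD compared to those without ASD". The Introduction says "we hypothesize the non-inferiority of Extended-Release Lithium Salts in adolescent patients with BD and ASD compared with those without comorbid ASD". Section 2.1 makes efficacy in patients with versus without ASD the primary aim.

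Section 2.6 describes two kinds of analysis. One is non-parametric testing of repeated scores, with the Wilcoxon signed-rank test as an example. The other is that "multiple linear regression models will be performed to detect the effect of the ASD diagnosis" on score changes, with age, gender, other psychotropic drugs and lithium plasma level as covariates.

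Section 2.5 uses the YMRS as the reference because "the YMRS score was the best available measure to determine the effect size that would be worth testing". It describes the calculation as a repeated-measures comparison of mean differences between two independent groups, and gives its settings as "establishing the error level at 0.05, power at 0.95, and effect size at 1.06". The result is 20 evaluable patients per group, raised to 25 per group for 20% dropout.

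No section gives a non-inferiority margin, a confidence-interval rule, the sidedness of the 0.05, or how a non-significant ASD effect will be interpreted.

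**The concern.** The hypothesis, the sample-size basis and the tests are all stated, and the last two do not answer the first. A signed-rank test asks whether scores change within patients and does not compare the groups. A regression meant to detect an ASD effect has no difference as its default null. Failing to reject that null does not show that ASD patients respond no worse than others by more than an acceptable amount.

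A small or noisy study is more likely to give a non-significant coefficient, so that result becomes easier to obtain as the evidence gets weaker. The Conclusions section says the findings could guide treatment of a highly vulnerable group, and section 2.2 selects patients for current self-injurious thoughts or behaviours. An unsupported statement that ASD patients do no worse would therefore matter.

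**Working it through.** **Inputs.** From section 2.5: effect size 1.06 (taken as a standardised mean difference), error level 0.05, power 0.95, 20 evaluable per group, 20% dropout. From section 2.3: equal group sizes. Assumed, because the protocol gives no figure: margins of 0.3 to 1.06 SD, a true difference of 0 for non-inferiority power, and no covariate adjustment. The SD of YMRS change is not given, so everything is in SD units.

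**Formula.** For n per group and standardised difference d, df = 2n − 2 and the noncentrality is d·√(n/2). One-sided power = 1 − F(t(1−α, df)), where F is the noncentral t distribution function. For n = 20, df = 38 and √(20/2) = 3.162.

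**1. The plan's own figure.** With d = 1.06 the noncentrality is 1.06 × 3.162 = 3.35.
- One-sided 5%: power is 0.950 at 20 per group, so the stated 40 reproduces.
- Two-sided 5%: power is 0.904 at 20 per group, and 95% power needs 25 per group.
- Dropout: 20 / (1 − 0.20) = 25 per group, 50 in total, which reproduces.

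Among two-sample t-tests, 40 is therefore the one-sided 5% result.

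**2. Precision at 20 per group.** Half-width = t × √(2/20) = t × 0.316.
- 95% interval: 2.024 × 0.316 = 0.64 SD.
- 90% interval: 1.686 × 0.316 = 0.53 SD.

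Both exceed 0.5 SD. Even an observed difference of exactly zero would typically fail to exclude a 0.5 SD margin.

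**3. Chance of a non-significant ASD effect when ASD patients truly do worse (20 per group).**

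| True deficit | Two-sided 5% | One-sided 5% |
|---|---|---|
| 0.3 SD | 85% | 76% |
| 0.5 SD | 66% | 54% |
| 0.8 SD | 31% | 20% |

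**4. Power of a non-inferiority test (20 per group, true difference 0).**

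| Margin | One-sided 5% | One-sided 2.5% |
|---|---|---|
| 0.3 SD | 24% | 15% |
| 0.5 SD | 46% | 34% |
| 0.8 SD | 80% | 69% |
| 1.06 SD | 95% | 90% |

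**5. Smallest margin for a given power (20 per group).**

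| Power | One-sided 5% | One-sided 2.5% |
|---|---|---|
| 80% | 0.80 SD | 0.91 SD |
| 90% | 0.94 SD | 1.05 SD |
| 95% | 1.06 SD | 1.17 SD |

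**6. If nobody dropped out (25 per group).** Power at a 0.5 SD margin is 54% (one-sided 5%) or 41% (one-sided 2.5%).

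**7. Size needed for a 0.5 SD margin at 80% power.** By the normal approximation, n = 2(z(1−α) + z(0.80))² / 0.5².
- One-sided 5%: 2 × (1.645 + 0.842)² / 0.25, giving 50 per group.
- One-sided 2.5%: 2 × (1.960 + 0.842)² / 0.25, giving 63 per group.

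**The case against.** **This is a condensed article, and a margin may sit in a fuller document.** That is fair for the margin alone. But the article does state its tests and its sample-size basis, and these address a different question from its hypothesis. A margin written elsewhere would also not make one of about 0.5 SD testable with 20 per group.

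**The regression already yields what is needed.** This stands in part. The model gives an adjusted ASD coefficient, from which a confidence interval follows. What is missing is the rule that turns the interval into a conclusion. The signed-rank test is only an example and is not offered as the group comparison, so little weight rests on it.

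**The sample size may already be a non-inferiority calculation.** This is the strongest point. A one-sided 5% t-test at d = 1.06 is numerically the same as a non-inferiority design with a 1.06 SD margin and true difference 0. It is therefore not established that section 2.5 planned a two-sided test for a difference. But section 2.5 calls 1.06 an effect size taken from literature on lithium-treated BD youths. It never calls it a margin and never states sidedness. As a margin, 1.06 SD would be very wide. If the figure reflects lithium's own effect (section 2.5 does not say which contrast it is), it could allow most or all of the benefit to be lost.

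**Nothing says a null result will be called non-inferior.** Correct. A reader might infer it because no other rule is offered, but the protocol contains no such decision rule and the inference should not be presented as the plan.

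**The study is a naturalistic cohort, and the Discussion calls for randomised confirmation.** True, and this favours a modest claim. It does not support keeping a non-inferiority claim without a margin.

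**Conclusion.** The point holds as a mismatch between the stated hypothesis and the stated analysis, and it should be corrected. With no margin or interval rule, the analysis as written cannot establish non-inferiority, and a non-significant ASD coefficient would be weak evidence for it.

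The size depends on an alpha whose sidedness the protocol does not state. A reader might conclude that every margin clearly below 0.9 SD is out of reach. That limit belongs to one-sided 2.5%; at one-sided 5%, the level that reproduces the stated sample size, it is 0.80 SD. A reader might also say that an important deficit would usually be missed. That is so for 0.3 and 0.5 SD in a two-sided test, but a 0.8 SD deficit is missed only 31% of the time, and the protocol sets no threshold of clinical importance.

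Under either alpha, power at a 0.5 SD margin stays below one half, and the stated size gives 95% power only for a margin of about 1.06 SD at one-sided 5%. These figures assume 20 analysed per group, no true difference for the power values, and no covariate adjustment, which could shift them somewhat.

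**What to change.** In section 2.6, state that non-inferiority will be concluded only if the confidence interval for the adjusted ASD minus non-ASD difference in YMRS change excludes a justified margin. Fix the margin in scale points in advance, and name the timepoint and the alpha (a 95% two-sided interval for one-sided 2.5%, or 90% for one-sided 5%). Add that a non-significant ASD coefficient is not evidence of non-inferiority. In section 2.5, state the sidedness, say whether 1.06 is meant as a margin, and re-derive the sample size for the margin chosen.

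If no defensible margin is as wide as about 0.8 to 0.9 SD, replace the claim of demonstrating non-inferiority in the Abstract and Introduction with estimating the difference in change and its 95% CI, and align section 2.6.

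The second route costs only wording and a more modest claim. The first also costs recruitment if the margin is tighter: at 0.5 SD and 80% power, 50 to 63 evaluable per group instead of 20.

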## 2. Materials and Methods

### 2.1. Study Design

This is a longitudinal prospective naturalistic comparative intervention study including BD youths with or without comorbid ASD, enrolled at the Department of Child and Adolescent Psychiatry and Psychopharmacology of our third-level hospital. This study will be conducted in accordance with the Declaration of Helsinki and approved by the Regional Ethics Committee for Clinical Trials of Tuscany (Pediatric Ethics Committee at Meyer Children’ Hospital of Florence). The aim of the study will be to evaluate the efficacy (primary aim) and tolerability (secondary aim) of Extended-Release Lithium Salts treatment in lithium-naïve adolescent patients with BD with versus without comorbid ASD. The STROBE (Strengthening the Reporting of Observational studies in Epidemiology) Statement Guidelines—Checklist for cohort studies will be followed to ensure an improved quality of reporting the results of our study.

### 2.2. Recruitment

Patients will be consecutively enrolled after assessment at our hospital for eligibility. Those who meet the eligibility criteria listed below will be included following a thorough clinical screening. All participants and their caregivers will be informed about the assessment procedure, and participation in the study will be voluntary. Recruited patients and their parents will be asked to provide their signed informed consent. Additionally, patients will be allowed to withdraw their consent any time during the study.

Inclusion criteria will be as follows: lithium-naïve adolescent inpatients or outpatients aged 12 to 18 years; informed consent obtained from the patient and both caregivers; diagnosis of Bipolar or Related Disorders (Bipolar Disorder type I (BD-I), Bipolar Disorder type II (BD-II), Cyclothymic Disorder, Other Specified or Unspecified Bipolar Disorder) with or without a diagnosis of Autism Spectrum Disorder according to the Diagnostic and Statistical Manual of Mental Disorders, Fifth Edition, Text Revision (DSM-5-TR); cognitive functioning within the borderline to normal range (i.e., Full-Scale Intelligence Quotient (FSIQ) or General Ability Index (GAI) ≥ 70); current presence of Self-Injurious Thoughts and/or Behaviors (SITB) (i.e., including non-suicidal self-injury (NSSI), intentional self-harm, suicide ideation, plans or preparations, or suicide attempts) as assessed through clinical interview (i.e., investigated by administering the Columbia—Suicide Severity Rating Scale); current presence of Emotional Dysregulation (ED) and/or irritability as assessed by means of standardized clinical measures (i.e., Reactivity, Intensity, Polarity, and Stability questionnaire for Youth and/or Affective Reactivity Index above the clinical cutoff). These latter criteria will be considered to ensure a relatively high clinical severity of the included sample.

Exclusion criteria will be as follows: patients under ongoing or previous treatment with lithium in any formulation; novel or unstable (i.e., modified posology) treatment with any other psychotropic drugs during the last six weeks; presence of intellectual disability; diagnosis of Schizophrenia Spectrum and Other Psychotic Disorders; presence of cannabis- or other substance-induced psychotic symptoms; females during pregnancy and/or breastfeeding; history of neuroleptic malignant syndrome and/or severe neurologic or neurodegenerative conditions; current diagnosis of epilepsy and/or history of seizures; any acute or unstable medical condition that may prevent study participation.

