## 4. Conclusions

This study will have the potential to make a significant contribution to the field. By investigating the efficacy and safety of Extended-Release Lithium Salts in a previously under-investigated population, it may provide critical evidence to guide clinical practice and inform future research. The study findings could pave the way for more personalized treatment approaches for adolescents with BD and comorbid ASD, ultimately improving outcomes for this vulnerable population. Specifically, if the results show that lithium offers advantages over harmful BD-related outcomes in youth with ASD, such as suicidality, while maintaining a manageable side effect profile, our study will assist clinicians in considering this often overlooked treatment option for this highly vulnerable group.

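### Before-after falls on C-SSRS, RIPoSt-Y and ARI are biased toward improvement, because the T0 assessment that selects severe patients is also the baseline and no group goes without lithium

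*Protocol article*

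**What the plan says.** **Entry (protocol article, 2.2).** Patients must have "current presence of Self-Injurious Thoughts and/or Behaviors (SITB"), which is "investigated by administering the Columbia—Suicide Severity Rating Scale". They must also have emotional dysregulation and/or irritability, shown by the RIPoSt-Y, that is the Reactivity, Intensity, Polarity, and "Stability questionnaire for Youth and/or Affective Reactivity Index above the clinical cutoff". The stated purpose is severity: "These latter criteria will be considered to ensure a relatively high clinical severity of the included sample".

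**Baseline (2.3).** "At T0, patients will be screened for eligibility and carefully evaluated". The outcome measures are also first taken at T0, before treatment starts. C-SSRS, RIPoSt-Y and ARI are on the list for T0, T1 and T2. No second pre-treatment reading is described.

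**Outcomes and treatment.** The abstract lists suicidality and emotional dysregulation among four primary domains. Section 2.1 makes efficacy the primary aim. Both groups receive lithium (2.3).

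**Analysis (2.6).** "Non-parametric tests for repeated measures (e.g., Wilcoxon signed rank test) will be used to analyze the psychiatric assessment score variations". Linear regression on the score changes then estimates the effect of the ASD diagnosis.

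**Interpretation.** Section 3 lists the lack of randomisation and of a control medication as limits on generalizability that call for randomised trials. Section 4 looks ahead to the case "if the results show that lithium offers advantages over harmful BD-related outcomes in youth with ASD, such as suicidality".

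**The concern.** A patient chosen because a fluctuating score is high today will on average score lower later, whatever is done in between. If the qualifying reading is also the baseline, that drop is counted as change under treatment. Here this applies directly to C-SSRS, RIPoSt-Y and ARI, which serve two of the four primary domains. A group not receiving lithium would show how large the drop is without the drug, but there is none.

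At stake is how a significant signed-rank result would be read. A reader could take a fall in suicidality or irritability among ASD patients as evidence that lithium works, when part or all of it may come from selection and natural course. Section 3 treats the missing control as a limit on generalizability. The problem here is internal validity, which it does not mention.

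**Working it through.** **1. The chain in the text.** The same instruments serve entry and outcome (2.2, 2.3). T0 is both the screen and the baseline (2.3). The test is before-after (2.6). All patients take lithium (2.3). The direction of the bias follows for any T0-T2 correlation below 1.

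**2. Inputs.** The plan gives no figure for this point, so there is none to reproduce.
- From 2.5: 20 evaluable patients per group.
- From 2.2: the RIPoSt-Y/ARI rule is and/or, so a patient may qualify on either scale.
- Not in the document, so assumed: T0-T2 correlation r; correlation b between the two scales at T0 (0.3 to 0.5); share s of the referred population above the cutoff on each scale. Scores are normal with SD 1 and no average drift in the unselected population. Given a scale's own T0 value, the other scale adds nothing to the prediction of T2. The drug effect is zero.

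**3. Expected fall on one scale.** With cutoff z-value c, normal density φ and distribution function Φ:

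fall = (1 − r) × (1 + b) × φ(c) × Φ(c√[(1 − b)/(1 + b)]) / P(at least one scale above c)

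For r = 0.6:

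| s | b | Mean T0 excess | Fall = 0.4 × excess |
|---|---|---|---|
| 50% (c = 0) | 0.3 | 0.259/0.702 = 0.370 | 0.15 SD |
| 50% | 0.5 | 0.299/0.667 = 0.449 | 0.18 SD |
| 30% (c = 0.524) | 0.3 | 0.294/0.472 = 0.622 | 0.25 SD |
| 30% | 0.5 | 0.323/0.443 = 0.728 | 0.29 SD |

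**4. Chance of a falsely significant improvement.** Signed-rank test, n = 20, two-sided 5%, counted only when the change is downward (nominal 2.5%), 20,000 simulated studies per setting:
- r = 0.6, s = 50%: about 10% (b = 0.3) to 13% (b = 0.5).
- r = 0.6, s = 30%: about 22% to 28%.
- Over r from 0.5 to 0.8 and s from 70% to 15%: about 4% to 62%.

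Other runs of the same model gave 10-12%, 25-31% and 3-59%, so only the order of magnitude should be read from these.

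**5. C-SSRS.** Current self-injurious thoughts or behaviour is required of everyone, with no alternative route. Any presence/absence summary therefore starts at 100% and can only fall. If 6 of 20 patients no longer had it at follow-up, an exact paired test would give p = 2 × 0.5⁶ = 0.031. This only illustrates the ceiling; 2.6 names no such test.

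**6. The between-group contrast.** With the same filter, r = 0.7 in both groups and equal population means, a t-test on change with 20 per group rejects in about 5% of null studies. The rate rises to 7-8% if one group's population mean is 0.5 SD higher, and to 10-25% if r is 0.6 in one group and 0.8 in the other. These rates use selection on the tested scale itself, which is stricter than the and/or rule.

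**The case against.** **The stated hypothesis is between groups.** The non-inferiority hypothesis, the aim in 2.1, the sample size in 2.5 and the regression in 2.6 all compare ASD-BD with BD-only. This stands. The problem is confined to the before-after tests, which is why it does not rank as a critical flaw.

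**The size could easily be overstated.** A reader might require every patient to exceed the cutoff on the scale being tested. With r = 0.6 that gives a fall of (1 − r)φ(c)/s = 0.32 SD (top 50%) or 0.46 SD (top 30%), and false improvement in about 35-37% or 61-64% of studies. The and/or rule does not support this: a patient can qualify on one scale and be unremarkable on the other. For RIPoSt-Y and ARI, a spurious significant fall is thus inflated above nominal but not shown to be likely. The ARI covers the last six months (2.4), which may dampen fluctuation further on that scale.

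**Suicidality figures.** A reader might also infer that a significant fall in suicidality is nearly certain. That needs a presence/absence test the plan does not name and remission rates the document does not give. C-SSRS severity, intensity and frequency can rise as well as fall from T0.

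**Section 4 is conditional.** It does not say that its conclusion would rest on the within-ASD change. A reader could take it that way, but the text does not commit to it.

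**Limitations are partly stated, and labelling may sit elsewhere.** Section 3 does admit the lack of randomisation and of a control medication, and calls for randomised trials. A fuller protocol or SAP may set the status of each test. However, the entry rule, the shared T0 reading, the before-after test and the absence of a lithium-free group are all fixed in this article, and nothing in it warns against reading the fall as efficacy.

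**Conclusion.** The point holds for the within-group tests on C-SSRS, RIPoSt-Y and ARI. Their falls from T0 are biased toward improvement by selection on T0 severity and by natural course, and cannot alone establish that lithium is effective. Other scales, such as YMRS, CDRS and MOAS, are affected by this selection only through their correlation with the entry scales.

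The direction is certain for any T0-T2 correlation below 1. The size is not, because the document gives no retest correlation, SD or cutoff position. Under the assumptions shown, false improvement on a RIPoSt-Y or ARI type scale is several times nominal in the central settings and close to nominal at the favourable end. The size for C-SSRS scores was not modelled. The ASD versus BD-only contrast is largely, though not completely, protected: it stays clean only if the groups have similar score stability and population severity. Severity: moderate.

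**What to change.** **Section 2.6.** Report within-group change on C-SSRS, RIPoSt-Y and ARI descriptively, as an estimate with a confidence interval labelled as change during lithium treatment. Base inference on the between-group comparison.

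**Sections 3 and 4.** State that selection on T0 severity and natural course cannot be separated from a lithium effect, and that this limits internal validity as well as generalizability. Do not attribute a before-after fall in suicidality to lithium.

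**Optional.** If feasible, repeat the entry scales after eligibility is confirmed and before treatment starts, and use that reading as baseline. This reduces regression to the mean but does not remove natural course.

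**Cost.** The required changes are wording only; sample size, visits and treatment stay as they are. The price is a less favourable efficacy statement. The optional repeat adds a short extra assessment.
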